## Abstract

**Background:**

^99m^Tc-NTP 15-5 is a SPECT radiotracer targeting proteoglycans (PG), components of the cartilaginous extracellular matrix. Imaging of PGs would be useful for the early detection of cartilage disorders (osteoarthritis, arthritis and chondrosarcoma, Aromatase Inhibitor associated arthralgia (AIA) in breast cancer), and the follow-up of patients under treatment. According to preclinical study results, ^99m^Tc-NTP 15-5, is a good candidate for a specific functional molecular imaging of joints. We intend to initiate a first in-human study to confirm and quantify ^99m^Tc-NTP 15-5 uptake in healthy joints.

**Methods:**

As the clinical development of this radiotracer would be oriented toward the functional imaging of joint pathologies, we have chosen to include patients with healthy joints (unilateral osteoarthritis of the knee or breast cancer with indication of AI treatment). This phase I study will be an open-label, multicenter, dose-escalation trial of a radiopharmaceutical orientation to determine the recommended level of activity of ^99m^Tc-NTP 15-5 to obtain the best joint tracer contrasts on images, without dose limiting toxicity (DLT). The secondary objectives will include the study of the pharmacology, biodistribution (using planar whole body and SPECT-CT acquisitions), toxicity, and dosimetry of this radiotracer. The dose escalation with 3 activity levels (5, 10, and 15 MBq/kg), will be conditioned by the absence at the previous level of DLT and of a visualized tracer accumulation on more than 80% of healthy joints as observed on scintigraphy performed at ≤ 2 h post-injection.

**Discussion:**

This first in-human phase I trial will be proof-of-concept of the relevance of ^99m^Tc-NTP 15-5 as a cartilage tracer, with the determination of the optimal methodology (dose and acquisition time) to obtain the best contrast to provide a functional image of joints with SPECT-CT.

**Trial registration number:**

Clinicaltrials.gov: NCT04481230. Identifier in French National Agency for the Safety of Medicines and Health Products (ANSM): N°EudraCT 2020-000495-37.

## Introduction

Biomechanical joint function depends on cartilage integrity. For many years UMR 1240 INSERM has developed a nuclear medicine imaging strategy targeting cartilage proteoglycans *in vivo*, such as ^99m^Tc-NTP 15-5. This radiotracer is a bifunctional agent which contains in its structure a polyazamacrocycle to complex ^99m^Tc and a positively charged quaternary ammonium (QA) function for binding to glycosaminoglycans of proteoglycans, components of the cartilaginous extracellular matrix (1). This radiotracer has emerged as a promising candidate for single-photon emission computed tomography (SPECT) imaging in nuclear medicine for specific, relevant, and functional molecular imaging of cartilage (2, 3). When intravenously administered to healthy rodents or lagomorph animals, ^99m^Tc-NTP 15-5 has been observed to accumulate markedly within articular cartilage with high *in vivo* stability (4, 5). The potential of the radiotracer to bind to cartilage has also been confirmed *ex vivo* on human knee specimens (3). A selective, intense accumulation was confirmed in cartilaginous tissue. In addition, areas of deficit in tracer uptake were clearly localized in anatomical areas of altered and eroded cartilage as seen in osteoarthritis specimens (3). Numerous preclinical studies have shown its relevance in molecular imaging of cartilaginous pathologies such as osteoarthritis (2, 4), inflammatory disease (6), and chondrosarcoma (7). ^99m^Tc-NTP 15-5 nuclear imaging was recently used in the murine destabilization of medial meniscus models, to monitor *in vivo* cartilage remodeling in response to disease-modifying osteoarthritis drugs (DMOAD) (8). Diagnosis of cartilaginous biochemical alterations could enable *in vivo* studies of joint functionality (9), which cannot be evaluated by conventional imaging techniques such as CT and MRI (10, 11). In addition, these conventional imaging techniques have poor diagnostic performances in early-stage osteoarthritis, which is a real public health problem (12–15). Functional articular cartilage imaging is of interest in joint treatment-related toxicities, such as Aromatase Inhibitor-Arthralgia (AIA). Aromatase inhibitors (AIs) are standard care for the adjuvant treatment of early hormone-sensitive breast cancer. However from 20% to 50% of women experience joint pain under AI treatment, with up to 20% treatment discontinuation for this toxicity which can compromise the effectiveness of these therapies (16, 17).

As the clinical development of this radiotracer would be oriented toward the functional imaging of cartilage in degenerative cartilage pathologies, we intend to carry out this first clinical proof-of-concept study on this radiotracer among patients (osteoarthritis and breast cancer) rather than among healthy volunteers. The evaluation of this radiotracer in this population (patients with unilateral osteoarthritis or patients with breast cancer with an indication for adjuvant AI treatment) will make it possible to verify: i) its binding to healthy joints, and ii) specific conditions enabling an initial evaluation of osteoarthritic joints.

This CARSPECT trial is thus a first in-human clinical study designed to confirm tracer accumulation in healthy cartilage joints. The main objective is to determine the recommended dose (activity in MBq/kg) of ^99m^Tc-NTP 15-5 to optimize joint fixation contrast on scintigraphy acquisitions, avoiding any toxicity. The secondary objectives relate to pharmacology, biodistribution, toxicity, and dosimetry evaluation. Differences in tracer accumulation between healthy and degenerative joints will also be assessed visually and quantitatively.

## Methods and analysis

### Study design

This “first in-human” phase I study is an open-label, multicenter, dose-escalation trial on a radiopharmaceutical tracer. The main objective is to identify, among three levels of ^99m^Tc-NTP 15-5 activity, the *recommended* (accurate) dose to detect tracer accumulation in a sufficient number of healthy joints, avoiding any toxicity.

Dose escalation will include 3 activity levels: 5, 10, and 15 MBq/kg. The initial dose of 5 MBq/kg will be used as the first level. The dose escalation scheme will allow dose escalations of one level conditioned by the absence, at the previous level, of dose-limiting toxicity (DLT) and the presence of tracer accumulation in healthy joints appearing on scintigraphy performed at ≤ 2 h post-injection (Figure 1). With a semi-quantitative visual scale, a score of 3 for at least 80% of healthy joints was chosen because it corresponds to a sensitivity of 80%, considered sufficient for diagnostic imaging.

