### Study objectives and endpoints

#### Primary objective and endpoint

The objective of this phase I trial is to determine the recommended dose (activity in MBq/kg) of ^99m^Tc-NTP 15-5 corresponding to an optimal joint tracer contrast, analyzed on a semi-quantitative visual scale.

The tracer accumulation observed (whole body imaging) on healthy joints (according to clinical evaluation by rheumatologist) (*n* = 31) of the wrists, elbows, shoulders, lumbar, and spine joints, C6-C7, hips, knees, and ankles will be scored on a semi-quantitative visual scale using three levels:

Lower level of fixation than the adjacent diaphyseal uptake,Fixation level equal to the adjacent diaphyseal uptake,Fixation level higher than the adjacent diaphyseal uptake.

The visual analysis will be performed by 2 nuclear physicians with reconciliation of the results. In case of disagreement, consensus will be reached *via* a joint reassessment.

For each patient, the ratio of the number of healthy joints scored at level 3 to the total number of healthy joints studied will be calculated.

The recommended dose will be defined as the dose at which 100% of patients present a score of 3 in at least 80% of healthy joints as seen on scintigraphy performed at 2 h post-injection or less, and without DLT. DLT is defined as any grade 3–4 toxicity occurring in the week following the injection.

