### Statistical considerations

A maximum of 6 patients should be included.

The number of subjects to be included takes into account the population selected and makes it possible to validate the hypothesis that healthy cartilage will present a significantly higher fixation than the adjacent diaphyseal fixation. For each patient, 31 observations (healthy joints) at 4 different times will be available for the evaluation of the main objective.

The optimal level of activity will be chosen using the dose escalation algorithm (Figure 1). The recommended dose will be defined as the dose from which 100% of patients present a score of 3 in at least 80% of healthy joints as observed on scintigraphy performed 2 h post-injection or less, and without DLT. If more than one time period (30 min or 2 h) meets these conditions, to choose the optimal time, we will perform a McNemar test where the number (minimum 2 patients, providing *n* ≥ 62 healthy joints) provides a power of 0.8, with an average effect size of 0.3 and an alpha risk of 0.05. For the moment, we do not have any element enabling estimation of the correlation with each patient.

Due to the nature and the design of the study, statistical analyses will be mainly descriptive. Missing data will not be replaced. The statistical significance threshold is set at 5%. Statistical analyses will be performed using R software.

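### The Abstract and the Study design section state the imaging condition for escalation with opposite sign, so a level with high uptake and no DLT escalates under one text and not under the other.

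*Protocol article*

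**What the plan says.** Two places give the condition for going up one level among 5, 10 and 15 MBq/kg.

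- **Abstract, Methods.** Escalation is "conditioned by the absence at the previous level of DLT and of a visualized tracer accumulation on more than 80% of healthy joints", as seen at 2 h or less.
- **Study design.** Escalation is conditional on the absence, at the level before, of "dose-limiting toxicity (DLT) and the presence of tracer accumulation in healthy joints appearing on scintigraphy", again at 2 h or less, with a pointer to Figure 1. The next sentence adds that "a score of 3 for at least 80% of healthy joints was chosen because it corresponds to a sensitivity of 80" percent, but it does not say that this threshold is part of the escalation condition.

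Two further places define the recommended dose without restating the escalation condition. Primary objective and endpoint calls it "the dose at which 100% of patients present a score of 3 in at least 80% of healthy joints", at 2 h or less and without DLT. Statistical considerations repeats this criterion with a small change of wording (*from which* for *at which*) and says that the level is chosen by the algorithm in Figure 1.

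Study design also gives the termination rule: at least 2 patients, one from each group, must have received the recommended level. The trial has at most 6 patients, and at most 4 per level.

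**The concern.** In the Abstract, the repeated *of* puts both items under *absence*: no DLT, and no accumulation above the threshold. In Study design, *the presence* stands parallel to *the absence*: no DLT, and accumulation seen. The sign of the imaging condition is reversed.

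This rule decides which activity the next patient receives and, through that, which level can be declared recommended, which is the primary objective. With at most 6 patients and termination possible after 2 at the recommended level, one escalation decision can affect a third or more of the trial (2/6 = 33%). Trial status says recruitment is under way.

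**Working it through.** The plan gives no figure to reproduce, because the point concerns the logic of a rule. The check lists every possible result for one patient and compares the decisions.

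**Inputs.** 31 healthy joints per patient (Primary objective and endpoint; Statistical considerations). Thresholds: more than 80% (Abstract) and at least 80% (Study design; Primary objective and endpoint; Statistical considerations). Let k be the number of joints showing uptake at 2 h or less, k = 0 to 31, with no DLT. I assume that visualized accumulation in the Abstract and tracer accumulation in Study design both mean a joint at score 3.

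**Threshold in joints.** 0.80 × 31 = 24.8. The first whole number that is at least 24.8 is 25, and the first that exceeds it is also 25. Check: 24/31 = 77.4% and 25/31 = 80.6%. Both wordings need 25 joints.

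**Decision rules.**

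- A, Abstract: escalate if k ≤ 24.
- C, Study design with no threshold in its escalation sentence: escalate if k ≥ 1.
- B, Study design with the 80% of its next sentence read in: escalate if k ≥ 25.
- D, Study design with *absence* forced to govern *the presence of* accumulation, and the 80% read in: escalate if k ≤ 24.

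| k of 31 | A: Abstract | C: any uptake | B: 80% read in | D: forced reading |
|---|---|---|---|---|
| 0 (0%) | escalate | no | no | escalate |
| 15 (48.4%) | escalate | escalate | no | escalate |
| 24 (77.4%) | escalate | escalate | no | escalate |
| 25 (80.6%) | no | escalate | escalate | no |
| 28 (90.3%) | no | escalate | escalate | no |
| 31 (100%) | no | escalate | escalate | no |

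**Count of conflicts with the Abstract over the 32 possible results.**

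- Reading C: k = 0 and k = 25 to 31, so 1 + 7 = 8 of 32.
- Reading B: all 32 of 32.
- Reading D: 0 of 32. This needs a phrase meaning the absence of the presence of accumulation, which the grammar of the sentence does not support.

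The results k = 25 to 31 and k = 0 conflict under both plain readings, B and C. The results k = 1 to 24 conflict only under B.

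**Against the recommended-dose definition.** If every patient at a level has k ≥ 25 without DLT, that level meets the definition in Primary objective and endpoint and in Statistical considerations. The termination rule is then met once 2 patients, one per group, have received it. Under the plain wording of Study design, the same result is what permits a move to the next level. A level with k = 0 and no DLT is neither recommended nor allowed to escalate under that wording.

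**The case against.** The strongest reply is that Figure 1 governs. Both Study design and Statistical considerations refer to it, it is not shown here, and neither is the approved protocol, version 5. The recommended-dose definition and the termination rule also bear on direction, so the likeliest explanation is a slip in one condensed sentence rather than two competing designs.

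Much of this stands. A reader might infer that the operative rule is undetermined, or that patients were allocated under conflicting rules. The documents do not support that, since the figure or the full protocol may state one direction clearly. What does not follow is that the point disappears. Whatever Figure 1 shows, the two plain statements cannot both match it. Condensing a protocol explains omissions, not two stated conditions of opposite sign. Inferring the direction from the recommended-dose definition still means choosing between two written rules.

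Three stronger readings also fail:

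- **That the texts conflict at every result.** This holds only if the 80% criterion is carried into the Study design escalation sentence, which itself contains no threshold.
- **That *more than* and *at least* 80% give different decisions.** At the planned 31 joints both need 25, and eligibility requires at least 31 healthy joints. The wording should match, but nothing turns on it.
- **That Primary objective and endpoint is a third version of the escalation rule.** It defines the recommended dose, which is a different decision, and the 2 h window is the same throughout.

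**Conclusion.** The contradiction is real and must be resolved, because at least one statement of the escalation condition is wrong as written. With no DLT, the two texts give opposite decisions for 25 to 31 of 31 joints and for 0 of 31, which is 8 of 32 possible results on the literal wording. That rises to 32 of 32 only if the 80% criterion is read into the Study design sentence. The results from 25 joints up matter most, because they are the ones that meet the recommended-dose criterion.

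The count of 8 or 32 describes possible results, not their probability. It rests on 31 evaluable joints, on score 3 as the meaning of accumulation, and on the plain grammar of both sentences. This review does not say which direction is right.

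**What to change.** Reconcile the Abstract and Study design with Figure 1 and with the recommended-dose definition in Primary objective and endpoint and in Statistical considerations. Write one escalation statement that gives:

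1. a single direction for the imaging condition, with the sponsor stating which one the approved protocol uses;
2. the same threshold wording as the recommended-dose criterion;
3. the same patient unit as that criterion, since neither escalation sentence says whether the condition applies to each patient or to all patients at the level.

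Use that statement wherever the rule appears. The cost is a wording correction to the article and, if the approved protocol carries the same conflict, a clarification there. No change to sample size, assessments or analysis is needed.

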**Figure 1 F1:**
[figure not shown]
Dose escalation plan of CARSPECT study.

A maximum of 6 patients will be included in the study. A maximum of 4 patients will be included per dose level. The rule for termination will be that at least 2 patients have received the recommended dose level, with one patient from each group in the selected dose level. Recruitment will be carried out alternately in each of the 2 groups (breast cancer patients/osteoarthritis patients) as far as possible.

The recruitment period will be 24 months, with a follow-up period of 1 week, for a total duration of 25 months.

### Coordination and participating institutions

The sponsor and body responsible for the coordination of the trial, data management, monitoring, and statistical analyses will be the Center Jean Perrin, Clermont-Ferrand.

The multicenter study is currently based at 2 sites in France: The University Hospital of Clermont-Ferrand and Center Jean Perrin. Patients with osteoarthritis will be recruited from the Rheumatology Department of the University Hospital of Clermont-Ferrand and patients with breast cancer will be recruited at the Jean Perrin Cancer Center. For all patients, radiopharmaceutical injections will be performed at the Nuclear Medicine Department of the Jean Perrin Cancer Center.

### Study objectives and endpoints

#### Primary objective and endpoint

The objective of this phase I trial is to determine the recommended dose (activity in MBq/kg) of ^99m^Tc-NTP 15-5 corresponding to an optimal joint tracer contrast, analyzed on a semi-quantitative visual scale.

The tracer accumulation observed (whole body imaging) on healthy joints (according to clinical evaluation by rheumatologist) (*n* = 31) of the wrists, elbows, shoulders, lumbar, and spine joints, C6-C7, hips, knees, and ankles will be scored on a semi-quantitative visual scale using three levels:

Lower level of fixation than the adjacent diaphyseal uptake,Fixation level equal to the adjacent diaphyseal uptake,Fixation level higher than the adjacent diaphyseal uptake.

The visual analysis will be performed by 2 nuclear physicians with reconciliation of the results. In case of disagreement, consensus will be reached *via* a joint reassessment.

For each patient, the ratio of the number of healthy joints scored at level 3 to the total number of healthy joints studied will be calculated.

The recommended dose will be defined as the dose at which 100% of patients present a score of 3 in at least 80% of healthy joints as seen on scintigraphy performed at 2 h post-injection or less, and without DLT. DLT is defined as any grade 3–4 toxicity occurring in the week following the injection.

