### Intervention

#### Study drug and administration

^99m^Tc-NTP 15-5 is synthesized by radioactive labeling with ^99m^Tc of the chemical precursor NTP 15-5, N-[(3-triethylammonio)propyl]- 1,4,7,10,13-pentaazacyclopentadecane, in presence of sodium pertechnetate (19). The synthesis of the pharmaceutical grade NTP 15-5 cold precursor is manufactured in accordance with GMP (Eras Laboratoire). The cold kit is manufactured in the experimental radiopharmacy unit in the Jean Perrin Center, in the form of a single-dose sterile kit.

The experimental drug is an injectable solution of ^99m^Tc-NTP 15-5with a molar activity greater than 2.5 GBq/μmol and radiochemical purity required to be over 90%.

According to the dose escalation plan, a single injection of 5, or 10, or 15 MBq/kg of ^99m^Tc-NTP 15-5 will be administered by slow intravenous injection on D0 in the presence of a nuclear medicine physician, without any premedication. Any treatment with NSAIDs will be discontinued at least 48 h before injection and can be resumed 24 h after injection. Prior and concomitant treatments will be collected at baseline and throughout the study.

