#### Study procedures and participant timeline

Before any study-related assessment starts, written informed consent will be obtained from each patient. At screening/baseline (within 15 days before administration of ^99m^Tc-NTP 15-5), the patients will have a clinical evaluation noting vital signs, ECG, a specialized consultation with a rheumatologist, blood and urine tests, and a pregnancy test (for women of childbearing age), and for patients with osteoarthritis, an evaluation of osteoarthritis by MRI and X-ray dating from less than 2 months prior.

After checking the eligibility criteria, a dose allocation request will be performed using an eCRF.

The ^99m^Tc-NTP 15-5 dose at an activity level of 5, or 10, or 15 MBq/kg (according to the dose escalation plan), will be injected on D0 with a follow-up of vital signs: before, and 5 min, 10 min, 15 min, 30 min, 1 h, 2 h, 4 h, and 6–8 h after the end of infusion.

*e In vivo* biodistribution of ^99m^Tc-NTP 15-5 will be assessed using:

- Whole-body planar scintigraphy acquisition 30 min, 2 h, 4 h, and 6–8 h after injection on D0; SPECT acquisitions at 1 h, 2.5 h, 4.5 h, and 6–8 h after injection on D0; Computed Tomography will be carried out before the injection or at the time of SPECT acquisition.- Blood samples for the pharmacokinetic study will be collected at 5 min, 10 min, 15 min, 30 min, 1 h, 2 h, 4 h, and 6–8 h post injection on D0. An 8-h urine collection will be performed for excretion evaluation.

Patients will be followed for 1 week with a visit on D8 for safety evaluation with clinical examination, vital signs, blood and urine analyses, and ECG.

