### Independent data monitoring committee

The IDMC will review all safety problems or other issues identified during the medical review and seek advice as needed. Experts in the IDMC performing this review will be selected for their relevant clinical trial/medical expertise. The committee will include a nuclear physician, a rheumatologist, and an oncologist. Given the very small number of DLTs expected, the committee will meet for each severe toxicity observed (grade ≥ 3).

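### The DLT definition stops at grade 4, so read literally it leaves a fatal (grade 5) toxicity outside the rule for escalation and the recommended dose

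*Protocol article*

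**What the plan says.** The definition is given once, under Primary objective and endpoint: "DLT is defined as any grade 3–4 toxicity occurring in the week following the injection".

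Two decisions depend on it:

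- **Escalation.** In Study design, moving up a level is "conditioned by the absence, at the previous level, of dose-limiting toxicity (DLT"), together with an imaging condition.
- **Recommended dose.** Primary objective and endpoint requires the chosen dose to be free of DLT, and Statistical considerations repeats this.

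Secondary objectives and endpoints names NCI-CTCAE version 4.03 as the grading scale.

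The Independent data monitoring committee section says "Given the very small number of DLTs expected, the committee will meet for each severe toxicity observed" and explains severe as grade 3 or above, with no upper limit. It also says "The IDMC will review all safety problems or other issues identified during the medical review".

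On timing, Study drug and administration says the tracer "will be administered by slow intravenous injection on D0". Study procedures and participant timeline says "Patients will be followed for 1 week with a visit on D8 for safety evaluation with clinical examination, vital signs, blood and urine analyses", and adds an ECG. Study design, in the text below Figure 1, describes the trial "with a follow-up period of 1 week, for a total duration of 25 months".

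**The concern.** A DLT definition is a decision rule, and its boundaries should be right as written. This one gives a closed range, grades 3 to 4, where an open one (grade 3 and above) is needed. On the named scale, the one category above that range is death. A patient whose toxicity is graded 5 would, on the literal wording, have no DLT.

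The rule has little slack. The trial takes at most 6 patients over three activity levels, with at most 4 at any level, and escalation requires that no DLT occurred at the previous level. One classification can therefore decide whether a level passes. In a first-in-human study, that classification should not depend on readers agreeing to look past the text.

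**Working it through.** The article gives no numerical figure to reproduce. The check is a comparison of grade sets, followed by a day count.

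**Grades**

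| Place in the article | Purpose | Grades covered |
|---|---|---|
| Primary objective and endpoint | DLT, governing escalation and recommended dose | 3, 4 |
| Independent data monitoring committee | Trigger for a committee meeting | 3 and above: 3, 4, 5 |

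Grades at or above 3 on the scale: {3, 4, 5}, three grades. Grades in the DLT definition: {3, 4}, two grades. Difference: {5}. The definition covers 2 of 3, and the missing grade is the fatal one. The article does not list the grades, so this step assumes the ordinary meaning of the scale it names.

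The second row is not a second DLT definition. It says when the committee meets. Its use here is limited: it shows that the article writes an open-ended threshold elsewhere, in a sentence that also mentions DLTs. It also shows that a grade 5 event would reach the committee. It does not say that such an event counts as a DLT, and no other text shown says so.

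**Window**

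- Injection is on D0, so one week ends at D0 + 7 = D7.
- The safety visit is on D8, and D8 − D7 = 1 day.
- The article says the tracer "will be injected on D0 with a follow-up of vital signs" at 8 times after injection (5, 10, 15 and 30 min, then 1, 2, 4 and 6–8 h), all on D0. The later safety examination, laboratory tests and ECG are described once, on D8.

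The one-day difference does not make a contradiction. The definition counts toxicity that occurs in the week, whatever day it is detected. A visit just after day 7 can look back over a completed week, and the article presents D8 as the visit belonging to the one-week follow-up. What remains open is narrow: a laboratory or ECG abnormality first seen on D8 has no earlier post-injection safety test to date its onset. It is worth saying that such a finding counts. This clarifies intent and is not a separate error.

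**The case against.** The strongest case on the other side is that nobody would misapply this rule. The stated aim is a dose that avoids any toxicity. A death would bring the committee together under its grade ≥ 3 trigger, the committee reviews all safety problems, and serious events are reported under local regulations. In this light, grade 3–4 is loose shorthand. The text is also a condensed article: the approved full protocol (version 5) and the content of Figure 1 are not shown, and either may be clearer.

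Most of this stands as an argument about impact, and it is why the point is small. It does not remove the point. The committee is given review, and is not said to reclassify an event under the escalation rule. The article does not leave the definition to another document either; it states the grade range and the window in full, and the grade range is wrong as stated.

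A reader might infer three stronger claims. None is supported:

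- **That the trial would escalate after a death.** The committee trigger, the reporting duty and the stated objective all point the other way.
- **That the committee threshold contradicts the DLT definition.** A meeting trigger may be broader than a DLT rule without inconsistency.
- **That D8 findings fall outside the window, leaving no laboratory safety assessment inside it.** This confuses the date of detection with the date of occurrence, and it ignores that the article ties the D8 visit to the one-week follow-up.

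**Conclusion.** The point holds for the grade range only. As written, the DLT criterion omits a fatal toxicity from the rule that governs escalation and the recommended dose. The size is one of the three grades at or above 3. The effect on an actual dose decision cannot be calculated from the article and is probably small, given the safeguards described and the very few DLTs expected.

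This rests on two assumptions: that grade 5 carries its usual meaning on the scale the article names, and that neither the full protocol nor Figure 1 states a different definition. If the full protocol already says grade ≥ 3, only the article's wording needs correcting. The timing of the D8 visit is not an error.

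**What to change.** Replace the definition with wording such as:

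> DLT is any grade ≥ 3 toxicity (NCI-CTCAE 4.03) arising within one week of injection, including abnormalities found at the scheduled D8 safety visit.

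The first part closes the gap at grade 5 and names the scale. The final clause records the evident intent about D8. The window should stay anchored to one week. Wording that runs it through to whenever the visit takes place would let a late visit lengthen the DLT period.

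The change adds no visit, test or patient and leaves the sample size unaffected. Its only downside is that an abnormality first seen at the D8 visit counts against the dose level, which is the cautious direction for a first-in-human study.
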